## 4. Study Methods

### 4.1. Randomisation and blinding

Having obtained consent, the randomising person collects the baseline data necessary to complete a randomisation form and enters the patient’s baseline data into our computerized central randomisation service by means of a secure 24/7 Web interface or a telephone call to the trial office during office hours. After the computer program has checked these baseline data for completeness and consistency it allocates that patient a unique study identification number and a treatment pack number which corresponds to either Fluoxetine or Placebo. The system applies a minimisation program to achieve balance for four factors:

- Delay since stroke onset [2 – 8 days v 9 – 15 days]
- Predicted outcome at 6 months based on Counsell 2002 [predicted probability of being alive & independent at 6 months of 0 – 0.15 v 0.16 – 1]
- Presence of a motor deficit [yes v no – where deficit is NIHSS5 (right or left) >0, NIHSS6 (right or left)>0 or NIHSS7 >0]
- Presence of aphasia [NIHSS question 9: 0 v 1 – 3 ]

The minimisation algorithm randomly allocates the first patient to a treatment, but allocates each subsequent patient to the treatment that leads to the least difference between the treatment groups with respect to the prognostic factors (Altman 2005). To ensure that we retain a random element to treatment allocation, patients will be allocated to the group which minimizes differences between groups with a probability of 0.8. The system contains a list of treatment codes for each centre and which match the stocks held at that centre. At the end of the session each patient is allocated a treatment code which corresponds to either an active (f.luoxetine 20mg once daily) or placebo treatment pack which contains six months supply of capsules held at that centre. The randomisation system will take account of the drug stocks held locally to firstly ensure the allocated treatment is available and second to minimise wastage.

The patient, their families, the healthcare team including the pharmacist and anyone involved in outpatient assessments will be blinded to the treatment allocation.

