### 7.4. Secondary outcomes - continuous

Where the outcome of interest is continuous, these will be compared between treatment groups using linear regression adjusting for factors in the baseline minimisation, or an alternative approach as necessary. This analysis will be conducted for the following outcomes at both six and twelve months.

1. Quality of life as measured by the EuroQol [EQ-5D]
2. Depression and anxiety as measured by the mental health inventory 5 [MHI-5 – question 21,22 of 6-month follow up; question 17,18 of 12-month follow up] and SIS [question 14 on 6-month follow up; question 10 on 12-month follow up].
3. Fatigue as measured by the vitality sub-scale of the Short Form (36) Health Survey [SF-36 question 20 on 6-month follow up; question 16 on 12-month follow up].
4. Limb strength as measured by SIS [question 12 on 6-month follow up; question 8 on 12-month follow up].
5. Hand function as measured by SIS [question 18 on 6-month follow up; question 14 on 12-month follow up].
6. Cognitive function as measured by SIS [question 13 on 6-month follow up; question 9 on 12-month follow up].
7. Communication as measured by SIS [question 15 on 6-month follow up; question 11 on 12-month follow up].
8. Extended ADL as measured by SIS [question 16 on 6-month follow up; question 12 on 12-month follow up].
9. Mobility as measured by SIS [question 17 on 6-month follow up; question 13 on 12-month follow up].
10. Social activity as measured by SIS [question 19 on 6-month follow up; question 15 on 12-month follow up].
11. Overall patient outcome as measured by the SIS total score
12. Overall recovery as measured by SIS thermometer [question 28 on 6-month follow up; question 24 on 12-month follow up].

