### 7.6. Pre-specified sub group analysis

Comparison of mRS at 6-months based on Ordinal analysis will be split by the following sub-groups: age [<70, ≥70], baseline probability of being alive and independent at 6-months [<0.15, 0.16-1 based on Carls model], type of stroke [ischaemic, haemorrhagic], patient able to provide own consent [yes, no] adjusting for baseline motor impairment [yes/no], baseline aphasia [yes/no] and baseline depression [yes/no].

Motor impairment: In patients with motor impairment resulting from the initial stroke [where motor impairment is defined as above] is there a difference in the motor function at 6 months [as measured by SIS, question 12, 17, 18 on follow up)]. Is this maintained at 12 months? Linear regression analysis will be performed on the baseline to 6-month change and separately for the 6-month to 12-month change both unadjusted and also adjusted for factors in the minimisation.*.*

Communication impairment: In patients with communication impairment resulting for the initial stroke [where communication impairment is defined as above on NIHSS] is there a difference in the communication function at 6 months [as measured by SIS, question 15]. Is this maintained at 12 months? This analysis will be performed unadjusted and also adjusted for factors in the minimisation.

Linear regression analysis will be performed on the baseline to 6-month change and separately for the 6-month to 12-month change both unadjusted and also adjusted for factors in the minimisation.

Mood: Is there a relationship between outcome [as defined by mRS at 6-months] and mood [measured using MHI5] and is this relationship affected by Fluoxetine?

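### The motor and communication analyses in SAP 7.6 adjust for a deficit factor that is constant in its own subset, so graded baseline NIHSS severity goes unused and precision is lost

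*SAP*

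**What the plan says.** Section 7.6 defines two analyses by restriction. The motor analysis is "In patients with motor impairment resulting from the initial stroke [where motor impairment is defined as above"]. The communication analysis is "In patients with communication impairment resulting for the initial stroke [where communication impairment is defined as above on NIHSS"]. For both, "Linear regression analysis will be performed on the baseline to 6-month change and separately for the 6-month to 12-month change", unadjusted and adjusted for the minimisation factors. The communication paragraph also states "This analysis will be performed unadjusted and also adjusted for factors in the minimisation".

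Section 4.1 lists four minimisation factors, each with two levels: delay since onset (2–8 v 9–15 days), predicted probability of being alive and independent at 6 months (0–0.15 v 0.16–1), "Presence of a motor deficit [yes v no – where deficit is NIHSS5 (right or left) >0, NIHSS6 (right or left)>0 or NIHSS7 >0"], and "Presence of aphasia [NIHSS question 9: 0 v 1 – 3"].

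Section 4.3.5 says that NIHSS items are graded (0 to 4, some 0 to 2 or 0 to 3) and summed to a total. Section 6.3 lists the total among the data on the randomisation form. The assessment schedule in section 4.2 has the SIS at weeks 26 and 52 only. No graded NIHSS score is named as a covariate anywhere in section 7.

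**The concern.** Restricting an analysis to patients who have a deficit, and then adjusting for whether they have it, adds nothing to the model. The covariate that ought to describe baseline motor or language status takes a single value in the analysis where it matters most. The trial nevertheless holds a graded measure of the same deficit, because the items must be scored to derive the yes/no factor. Patients with item 9 scores of 1 and 3, for example, share one aphasia code.

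Section 3 says that the effect on neurological function by specific baseline deficit is of particular interest, and these analyses use only part of the sample. If baseline severity predicts the 6-month SIS domain, leaving it out makes the confidence intervals wider than they need be. Minimisation balances the presence of each deficit and not its severity, so a chance difference in severity between the arms would also stay in the estimate.

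**Working it through.** The SAP gives no power, standard deviation, effect size or subset size for these analyses, so there is no stated figure to reproduce.

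**Step 1: structure of the model.** In the motor subset the adjusted model has six columns: intercept, treatment, motor deficit, delay, predicted outcome, aphasia. Under section 4.1 every patient in the subset has motor deficit = yes, so that column equals the intercept. Six columns have rank 5, and the motor factor drops out. In the communication subset the aphasia column (item 9 scored 1–3) equals the intercept in the same way.

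One qualification applies to the motor case. Section 3 describes a motor deficit as affecting face, arm or leg, whereas section 4.1 uses NIHSS items 5, 6 and 7. If the section 3 description governed, patients with facial weakness alone could be in the subset but coded no, and the factor would be nearly rather than exactly constant. The aphasia case is unaffected.

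**Step 2: other routes by which severity could enter.**
- Predicted outcome and the other deficit factor still vary within each subset and are related to severity, but each has only two levels and neither measures the deficit in question.
- A change from baseline would carry baseline status if the SIS were measured at baseline. It is not, so the baseline-to-6-month change cannot be computed as written.

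**Step 3: size of the loss.** Let r be the partial correlation between the graded NIHSS score and the 6-month SIS domain score, given the other factors. The documents give no value, so r is an assumption. Adding the covariate multiplies the residual variance by 1 − r². With two-sided alpha 0.05 (also assumed),

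power = Φ((1.960 + z₀)/√(1 − r²) − 1.960), where z₀ = 0.842 for a starting power of 80%.

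The number of extra patients needed for the same gain without the covariate is 1/(1 − r²) − 1.

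For r = 0.3: √0.91 = 0.954; 2.802/0.954 = 2.937; 2.937 − 1.960 = 0.977; Φ = 0.836.

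| r | 1 − r² | Equivalent extra patients | Power from 80% | Power from 90% |
|---|---|---|---|---|
| 0.2 | 0.96 | 4% | 81.6% | 91.1% |
| 0.3 | 0.91 | 10% | 83.6% | 92.5% |
| 0.4 | 0.84 | 19% | 86.4% | 94.3% |
| 0.5 | 0.75 | 33% | 89.9% | 96.3% |

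**Step 4: does predicted outcome already recover the gain?** A simulation of the motor subset (1,500 patients, 1,000 runs) used a prognostic index correlated 0.5 with severity and cut into two levels. When severity correlated 0.3 with the outcome, power was 0.82 with the minimisation factors and 0.85 with severity added. At 0.5 it was 0.82 and 0.90. The Monte Carlo standard error is about 1.2 points (√(0.82 × 0.18/1000) = 0.012). In this setting the two-level factor recovered little, but the result depends on the assumed correlations.

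**The case against.** The strongest reply is that the redundancy itself is harmless. A constant covariate drops out and distorts nothing, and the other three factors still adjust. Using the minimisation factors is the SAP's general rule, so adding covariates to a secondary subgroup analysis is an efficiency gain and not the repair of an invalid method. The prognostic model behind predicted outcome is in a figure that is not shown, so how much motor or language severity it carries is unknown. The size rests wholly on an assumed r. From a 90% start the gain is only 2.5 points at r = 0.3 and 4.3 at r = 0.4. Finally, the more basic fault is the missing baseline SIS, and any repair of that has to settle the baseline adjustment as well.

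Most of this stands, and it limits the point. A reader might infer that the planned comparison is biased. It is not: allocation is randomised within each subset, and only precision is at issue. A reader might also infer that mild and severe deficits are treated as wholly alike. They are not, because such patients can differ on predicted outcome and on the other deficit factor. Nor does the collinearity extend to section 7.4, where the deficit factors vary across all patients and the text allows an alternative approach.

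What the reply does not do is give the constant factor a function, or show that any other part of the plan uses the graded score. The balance check on total NIHSS in section 6.3 describes the groups without adjusting for the score. The missing baseline SIS strengthens the case, since it leaves the NIHSS items as the closest baseline measure of the outcome.

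**Conclusion.** The point holds as a loss of precision in the two deficit-restricted analyses of section 7.6. That the defining factor does no work in its own subset follows directly from sections 4.1 and 7.6: exactly for aphasia, and exactly for motor under the section 4.1 definition.

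The size cannot be fixed from the SAP. From an assumed 80% power, partial correlations of 0.2 to 0.5 give about 82% to 90%, equivalent to 4% to 33% more patients. This assumes a linear model for the 6-month score and a severity score that predicts it beyond the other factors. It would be tempting to call the loss material in this trial, but without a correlation or a starting power the documents do not establish that.

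The figures apply to the 6-month score. For the 6-to-12-month change the 6-month SIS is already subtracted, so baseline NIHSS is likely to add less.

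**What to change.** Amend section 7.6 before unblinding as follows:

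- Make the 6-month SIS domain score the response, in place of a change from a baseline that is not measured. Adding a covariate while keeping the present response would leave an outcome that cannot be computed.
- Motor analysis: drop the motor yes/no factor and adjust for the sum of NIHSS items 5, 6 and 7, plus delay, predicted outcome and aphasia.
- Communication analysis: drop the aphasia yes/no factor and adjust for NIHSS item 9 as levels, plus delay, predicted outcome and motor deficit.
- State which motor definition, that of section 3 or of section 4.1, sets the motor subset.

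The 6-to-12-month change can be computed and may stay. The same covariates can be used there, with less gain expected. Using them for limb strength, hand function, mobility and communication in section 7.4 is optional.

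The cost is SAP wording. The motor model uses one extra degree of freedom and the communication model two (item 9 has three levels within the subset); the dropped factors were using none. No new data are needed, provided that the item scores behind the minimisation factors were kept.

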### 7.7. Possible extra analyses

AFFINITY, EFFECTS and a Polish study are all running simultaneously to FOCUS, at the conclusion of these trials an individual patient meta-analysis may be carried out.

## 8. Revision History

| **Document version & date** | **Review comment** | Date of review | **Reviewer’s Signature** |
| --- | --- | --- | --- |
|  |  |  |  |
